**Fig. 1 Fig1:**
[figure not shown]
Participant time-line. Both conditions come to all assessment time points and take part in an Ambulatory Assessment. Ambulatory Assessment starts 1 day after the baseline assessment: for 40 consecutive days, signals are distributed six times a day (all items are listed in Additional file 2). *KIMS* Kentucky Inventory of Mindfulness Scale, *BFI-44* Big Five Inventory-44, *MAAS* Mindful Attention Awareness Scale, *SCS-K-D* Self-control Scale-K-D, *SDS-17* Social Desirability Scale-17, *WHO-5* World Health Organization Five Wellbeing Index, *BSI-18* Brief Symptom Inventory, *ERQ* Emotion Regulation Questionnaire, *AAS* Adult Attachment Scale, *DEBQ* Dutch Eating Behavior Questionnaire, *TMS* Toronto Mindfulness Scale. The post-intervention Feedback Questionnaire assesses effort that was expended during Ambulatory Assessment

### Study design and settings

The SMASH study is a randomized, controlled trial that combines an Ambulatory Assessment part of 40 consecutive days and seven weekly laboratory sessions during this period (see Fig. 1). Participants are randomized to either mindfulness training or a wait-list control condition: participants in both conditions attend the weekly laboratory sessions at the Institute of Psychology in Mainz completing self-report measures on habitual self-control and habitual mindfulness. In the intervention, participants additionally engage in intense computer-based mindfulness training.

### Eligibility criteria

Inclusion criteria are (1) the ability to understand and fluently speak German, (2) students (senior students included) aged between 18 and 65 years, (3) sufficient experience to operate a smartphone reliably and (4) having provided informed consent. Exclusion criteria are (1) the diagnosis of a psychiatric disorder and (2) any mental or somatic impairment that precludes the use of a smartphone.

### Intervention

The mindfulness training starts 1 week after the first laboratory meeting. From this time on, participants from the intervention and control conditions take part in different laboratory meetings (separated from each other) to minimize the chance of contamination between conditions. Mindfulness is practiced with a computer-based guided-breathing meditation for five weekly sessions in which one’s own breath has to be counted repetitively from one to nine [26]. A “click” sound occurs if a breath was miscounted guiding attention back to the current moment and the Breath-counting Task [26]. After the first mindfulness training session, participants in the intervention condition are also able to practice mindfulness (breathing meditation or body scan) at home by listening to an audio file via their smartphones. Each episode of ambulatory mindfulness practice is saved in a data file in order to assess how often mindfulness is practiced during the treatment period. After the third training session, participants perform an informal mindfulness task, which is used in mindfulness-based stress-reduction programs [15] to apply mindfulness in everyday life.

Since only healthy participants are enrolled in the SMASH study, we do not expect any harm from the low-level mindfulness intervention. For this reason, there are no criteria for discontinuing or modifying the intervention.

### Primary and secondary outcome measures

#### Momentary mindfulness

The first primary outcome of this trial is momentary mindfulness assessed via electronic diaries six times per day on 40 consecutive days between 10 a.m. and 8 p.m. with three selected items from the state version of the *Mindful Attention Awareness Scale* (MAAS; study 4 from Brown and Ryan [27]). The state version of the MAAS consists of five rephrased items drawn from the original MAAS (Items 3, 8, 10 13 and 14) in order to assess the degree of mindfulness experienced directly in daily life [27]. We chose only three items from the German MAAS [28] (Items 8, 10 and 14) to lower participants’ burden and adapting to the needs of an Ambulatory Assessment. The three items were rephrased according to Brown and Ryan [27].

#### Momentary self-control

The second primary outcome is momentary self-control which is measured via electronic diaries six times per day on 40 consecutive days between 10 a.m. and 8 p.m. with three items from the German version *State Self-control Capacity Scale* (SSCCS) [29]. The SSCCS consists of 25 items and assesses self-control capacity that is momentarily available for self-control execution (Cronbach’s *α* ≥ .93). For the SMASH study, the original SSCCS items 12, 16 and 18 were selected due to their high loadings on the SSCCS: “I can’t absorb any information,” “I want to give up,” “I feel like my willpower is gone.” The selected SSCCS items are complemented with items that were used by Hofmann et al. [7] (see Additional file 2: Table S1 and Table S2).

#### Habitual self-control

One of the secondary outcomes is habitual self-control which is measured with the brief *Self-control Scale* (SCS) consisting of 13 items [2]. The SMASH study uses the German Self-Control Scale-K-D (SCS-K-D) (Cronbach’s *α* = .79 (t1) and *α* = .80 (t2) and a test-retest reliability of *r* = .82) [30]. The SCS-K-D is answered at seven weekly meetings in order to measure changes in habitual self-control.

#### Habitual mindfulness

As a further secondary outcome, habitual mindfulness is assessed with the original version of the MAAS [27], which consists of 15 items. A validated German version of the MAAS is used in this study (Cronbach’s *α* = .83; test-retest reliability *r* = .82) [28]. The self-report of habitual mindfulness is collected at the seven weekly laboratory meetings.

### Additional measures

A range of demographic variables, self-report questionnaires and ambulatorily assessed measures were collected. All self-report and behavioral measures and their assessment time points are shown in Fig. 1 in overview.

#### Demographics

Participants are asked to report their (1) age, (2) gender, (3) highest graduation, (4) engagement in a religion, (5) Yoga practice and (6) substance use (alcohol, cigarettes, marijuana).

#### Self-report questionnaires

The frequency of *experienced desires* in daily life is measured with 15 desire domains [7, 8].

Also *goal commitment* is assessed by asking whether participants have planned to pursue 20 specific goals [7, 8] for the next 6 weeks. Personality traits are assessed with the German version of the *Big Five Inventory-44* (BFI-44) [31, 32], which consists of 42 items and five scales (Cronbach’s *α* = .63 to *α* = .86; test-retest correlation *r* = .55 to *r* = .82) [32]. Furthermore, social desirability is assessed with the *Social Desirability Scale-17* (SDS-17) [33, 34] (Cronbach’s *α* = .72; test-retest correlation *r* = .80) [34] consisting of 16 items.

Complementary to the MAAS, different aspects of mindfulness (observing, acting with awareness, acting without judgement, and describing) are assessed with the 39 items from the German *Kentucky Inventory of Mindfulness Skills* (KIMS) [35, 36] (Cronbach’s *α* = .79 to *α* = .92; test-retest correlation *r* = .78 to *r* = .86) [36]. Additionally, two factors of mindful experience (curiosity and decentering) are measured with the *Toronto Mindfulness Scale* (TMS) [37], which consists of 13 items (Cronbach’s *α* = .95).

Wellbeing is measured with the German version of the *WHO-5 Wellbeing Index* [38] consisting of five items (Cronbach’s *α* = .92 [39]). As another measure for psychological wellbeing, the German version [40] of the *Brief Symptom Inventory-18* [41] is additionally used to assess changes in syndromes of somatization, depression and anxiety with 18 items (Cronbach’s *α* ranges between *α* = .63 and *α* = .93) [40].

Moreover, habitual behaviors in several self-control domains are assessed. The use of two different emotion regulation strategies, reappraisal and suppression, is measured with the German version of the *Emotion Regulation Questionnaire* (ERQ) [42, 43] which consists of 10 items (reappraisal *α* = .76; suppression *α* = .74) [43]. Interpersonal relationships are measured with the German version of the *Adult Attachment Scale* (AAS) [44, 45] consisting of 15 items and the three scales of closeness, trust and fear (*α* = .72 to .79) [45]. The habitual eating styles restrictive eating, emotional eating and external eating are assessed with the *Fragebogen zum Ernährungsverhalten-II* (FEV-II, Cronbach’s *α* = .82 to *α* = .92) [46], the German version of the *Dutch Eating Behavior Questionnaire* (DEBQ) [47]. The FEV-II consists of 33 items.

In order to investigate affective dynamics, the measurement of affect is based on *Russell’s affective circumplex model* [48, 49]. Positive and negative affect are each assessed with four items.

#### Behavioral measures

As a behavioral measure of mindfulness, the *Breath-counting Task* is conducted [26]. During this task, participants have to count their breath for 18 min repetitively from one to nine. Additionally, participants are asked to press a button whenever they caught themselves miscounting their breath (self-caught misc﻿outing)﻿.﻿ Counting accuracy will be analyzed by calculating the percentage of correctly counted breath trials in relation to all trials (self-caught trials, miscounted trials and correctly counted trials). The breath counting is interrupted every 90 s on average in order to present two items, assessing momentary meta-awareness and mind wandering [26].

#### Ambulatory Assessment

Due to conditional branching in the presentation of items during the Ambulatory Assessment, participants answer 31 to 50 items (Additional file 2: Tables S1, S2 and S3) at each signal six times per day regarding (1) positive and negative affect [48, 49], (2) worrying [24, 50], (3) momentary emotion regulation strategies [12], (4) attention (item from previous research in our laboratory) and (5) situational circumstances (items from several Ambulatory Assessment prompts [8, 11, 12, 51]). If a participant indicates a specific desire, additional items appear on the smartphone screen depending on the indicated desire: for example, if a given participant indicates the desire “food”, items are presented that assess specific eating behaviors. Further additional items from the (6) DEBQ [47], (7) the *Situational Motivation Scale* [52], (8) the *Work-related Flow Inventory* [53], (9) the *State Adult Attachment Measure* [54], (10) the *Recovery Experience Questionnaire* [55] and items regarding (11) sexual behavior and (12) spending money are presented in Additional file 2: Tables S2 and S3. A pre-test (*N* = 6) showed that it takes about 2 min (*M* = 1.89; *SD* = 1.84) to complete the presented questionnaires after each signal.

At the time point of study enrollment, there was no method that could model different types of variables in a network. Due to the chosen mode of statistical analysis (network approach) that includes VAR and multilevel regression models, ambulatorily assessed variables all had to be either continuous or binary variables. For this reason, all originally binary variables were changed into continuous variables.

### Procedure

A participant time-line of enrollment, intervention and assessments is presented in Fig. 1. During a first laboratory session, a research assistant conducts a screening interview to check for inclusion and exclusion criteria. Eligible participants are invited to give their written consent for study participation (see Additional file 3). Afterwards, allocation takes place. Participants are free to withdraw their consent to participate anytime without any consequences.

#### Laboratory sessions

During the first laboratory session, all participants complete self-report questionnaires and a Breath-counting Task [26] which is conducted on computer. One week after the first laboratory meeting, both intervention and control condition participants come to five weekly laboratory meetings completing questionnaires regarding self-reported dispositional mindfulness and self-control. A maximum of three participants can take part in a laboratory meeting at once. From the second laboratory meeting on, only the intervention condition starts practicing mindfulness with a computer-based guided-breathing meditation for 12 min at five weekly appointments. At the seventh and final laboratory meeting, a post-intervention measurement takes place. During the final measurement, questionnaires that were completed within the first laboratory meeting are answered again. Also the Breath-counting Task [26] is conducted by both control and intervention conditions comparing counting accuracy between them as well as before and after mindfulness training. The seven laboratory meetings are conducted on computers with the operating system OS X El Capitan, Version 10.11 and a screen resolution of 1920 × 1080. The software Inquisit 4 (Millisecond Software, 2014) is used to present the questionnaires on the screen.

#### Ambulatory Assessment protocol

A day after the first laboratory session, the Ambulatory Assessment begins (day 1 till day 40). Each day, signals are randomly distributed six times a day via smartphones throughout a defined timeframe of 10 h. Signals can occur between 10 a.m. and 8 p.m. This time span is divided into blocks of 2 h [56], defining for each block that two consecutive signals could be at least 45 min apart. Throughout a timeframe of 5 min after a signal, participants can start, reject or postpone their answer for 15 min. Participants are asked to complete short questionnaires which assess experiences at the present moment or within the last 30 min [7].

Moto E (second generation) smartphones with the latest Android Lollipop version 5.1 are handed to participants in case they do not own an Android-based smartphone. Ambulatory Assessment is run via the application movisensXS, version 0.8.4203 (movisens GmbH, Karlsruhe, Germany), which has to be downloaded and installed either on the personal or the received smartphone. This app schedules the beeping signals, presents the questionnaires on the smartphone and saves collected data by uploading it to a secured server.

### Sample size

The sample size was calculated with a power calculation formula for multilevel models [57] to detect group differences in state and trait mindfulness between individuals. Based on previous research in our laboratory, we assume an unexplained intraclass correlation (ICC) of 0.25 and want to achieve a power of 1 − *β* = .95 and set an alpha level *α* = .05 for a two-sided test to detect a medium difference of Cohens’s *d* = .33 between conditions. The expected medium effect size is based on a meta-analysis (medium effect size Hedge’s *g* = .33) comparing mindfulness-based therapy treatment with other active treatments [58] – since the wait-list control condition participants take part in an Ambulatory Assessment and come to weekly laboratory meetings during its waiting period, we considered the wait-list control condition as an active treatment condition as a conservative estimate for our power calculations rather than an inactive waiting condition. Thus, this leads to a sample size of *N* = 120 to detect medium group differences between individuals. Since prior Ambulatory Assessments in our department showed attrition rates of approximately 10%, the SMASH study aims at a sample size of *N* = 134 to achieve a final total *N* = 120 (control condition *n* = 60; mindfulness intervention *n* = 60).

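### The 95% power stated for state and trait mindfulness is reproduced only for mean momentary mindfulness over many prompts; at the stated ICC it does not carry over to trait mindfulness, measured seven times

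*Protocol article*

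**What the plan says.** The Sample size section describes a multilevel power formula used "to detect group differences in state and trait mindfulness between individuals". Its inputs are given once, for both outcomes. For the correlation, the authors write: "we assume an unexplained intraclass correlation (ICC) of 0.25". The effect is worded as follows: "to detect a medium difference of Cohens’s *d* = .33 between conditions". The test is two-sided at the 5% level, with a target power of 95%. The effect size comes from a meta-analysis "comparing mindfulness-based therapy treatment with other active treatments", with g = .33. The result is N = 120 (60 per arm), raised to 134 for 10% attrition. The section gives no number of repeated measurements and does not say which SD d is scaled on.

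Elsewhere in the protocol article:

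- Momentary mindfulness is a primary outcome, recorded six times a day on 40 days.
- Habitual mindfulness is a secondary outcome: "The self-report of habitual mindfulness is collected at the seven weekly laboratory meetings". Its scale has "test-retest reliability *r* = .82".
- Under Primary and secondary outcome analysis, the habitual outcomes are tested by the interaction of the seven meetings with group in a mixed model.

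**The concern.** In a multilevel formula of this kind, the required N depends on how many measurements each person contributes and how strongly they correlate. The two outcomes differ on both. One has up to 240 prompts and the other seven questionnaires, and a trait scale is usually far more stable from week to week than a momentary rating. A single ICC and a single N are unlikely to give the same power for both.

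The scale of d also matters. If d is a fraction of the spread of single prompts, the same .33 is a larger difference when expressed in SDs of persons' long-run means.

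Habitual mindfulness is a named secondary outcome. Readers of its result, a null result in particular, would take the 95% at face value.

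**Working it through.** **Inputs.** From Sample size: ICC ρ = .25, d = .33, two-sided α = .05, power .95, 60 per arm. From the outcome sections: m = 6 × 40 = 240 prompts at full compliance for state, m = 7 for trait, and trait test-retest r = .82. All results are normal approximations.

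**Formula for a difference in person means.** With d scaled on the SD of a single measurement,

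N = 4(1.960 + 1.645)² / d² × F, where F = ρ + (1 − ρ)/m.

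For d = .33 the first factor is 4 × 12.995 / 0.1089 = 477.3. Power at 60 per arm is Φ(z − 1.960), with z = .33 / √(F × 2/60).

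**1. Reproducing the plan's figure (state).** With m = 240, F = .25 + .75/240 = .2531. Then N = 477.3 × .2531 = 120.8, z = 3.59 and power is 94.9%. The exact number of prompts matters little: power is 94.5% at m = 100 and 93.7% at m = 40. The attrition step also reproduces: 120/.90 = 133.3, rounded up to 134. With m = 1, or with d scaled on the SD of person means, N would be about 478.

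**2. What d = .33 then means.** At ρ = .25 the between-person SD is √.25 = .5 of the single-prompt SD, so .33 single-prompt SD equals .33/.5 = 0.66 between-person SD. If the cited g = .33 is instead read on the between-person SD, which is an assumption, z = .33/√(2/60) = 1.81 and power is about 44%.

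**3. Trait, difference in mean level over seven measurements.**

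| Within-person correlation | F | Power at N = 120 | N for 95% (unrounded) |
|---|---|---|---|
| .25 (Sample size section) | .357 | 85.6% | 170.5 |
| .50 | .571 | 66.7% | 272.7 |
| .70 | .743 | 55.5% | 354.6 |
| .82 (test-retest r) | .846 | 50.2% | 403.7 |

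**4. Trait, the planned meeting-by-group interaction.** Assume compound symmetry and a group difference that grows linearly from 0 at meeting 1 to .33 SD at meeting 7.

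- *Linear slope (1 df).* The slope difference is .33/6 = .055 per meeting. The sum of squared meeting deviations is 28, so z = .055 / √[(1 − ρ)/28 × 2/60].
- *Categorical meeting (6 df).* The noncentrality is λ = 28 × .055² / [(1 − ρ) × 2/60] = 2.541/(1 − ρ), referred to a noncentral chi-square with 6 df.

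| Within-person correlation | Linear: z, power | 6 df: λ, power |
|---|---|---|
| .25 | 1.84, 45% | 3.39, 23% |
| .82 | 3.76, 96% | 14.12, 82% |

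The correlation acts in opposite directions in steps 3 and 4. A high value lowers power for the mean level and raises it for the interaction.

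**The case against.** The strongest defence is that the mean-level contrast is not the trait test that the trial plans. The plan tests meeting by group, for which a stable scale is an advantage. At a correlation of .82, a linear interaction reaches about 96%, so trait power may in fact be adequate. In addition, N = 120 and the increase to 134 both reproduce, trait mindfulness is a secondary outcome, and the formula's source and the scaling of the cited g are not in the documents.

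Much of this stands, and it rules out three stronger readings that a reader might infer.

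- *That trait power is a coin toss.* The 50% needs two things: a scale-validation test-retest correlation standing in for this sample's ICC, and a comparison of seven-meeting means that the plan does not use. It is one end of a range.
- *That the trial is powered for an effect twice the cited one.* This requires the meta-analytic g to be on the between-person SD. The documents do not say so, and a g from single observed scores would include within-person variance.
- *That N = 120 depends on exactly 240 prompts.* Any large number gives nearly the same power.

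The defence does not rescue the sentence in the Sample size section. That section describes a difference between individuals, not an interaction, and gives .25 as the only correlation. At .25 the interaction does worse than the mean level. The 96% needs a correlation that the calculation did not use, together with a linear effect of meeting.

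**Conclusion.** The concern holds as a misstatement of what the calculation covers; N itself reproduces. The 95% is supported for a difference of 0.33 single-prompt SD in mean momentary mindfulness over many prompts. It is not supported for trait mindfulness. At the stated ICC of .25, none of the trait tests examined reaches 95%: about 86% for the mean level, 45% for a linear interaction and 23% for a 6-df interaction. At .82 the same three are about 50%, 96% and 82%.

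The mean-level figures assume a constant difference of .33 single-measurement SD. The interaction figures assume compound symmetry and linear growth to .33 SD at meeting 7. Using .82 as a within-person correlation is an assumption about this sample. The 240 prompts and the single-prompt scale are inferred because they reproduce N; the section states neither. The 44% for momentary mindfulness is conditional on reading g on the between-person SD.

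**What to change.** Keep N = 120 and the planned mixed-model analysis. In the Sample size section:

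1. State that the 95% refers to a difference of 0.33 SD of a single prompt in mean momentary mindfulness, and give the number of prompts assumed. Add that this equals 0.66 between-person SD at ICC .25.
2. Either delete trait mindfulness from the power claim, or add a separate power for the planned meeting-by-group test. The latter should state whether meeting is linear or categorical, the assumed course of the effect, the within-person correlation, and power over a range of that correlation.

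There is no reason to replace the planned interaction with a baseline-adjusted comparison at meeting 7. Under r = .82 that gives about 88% (variance factor 1 − .82² = .328), against about 96% for the linear interaction.

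The cost is a few sentences and a stated power for a secondary outcome that may look less favourable. It needs no more participants or measurements.

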### Primary and secondary outcome analysis

First, the effect of mindfulness training on momentary mindfulness and self-control will be explored. Since Ambulatory Assessment data have a hierarchical structure, where several observations are nested within each day and days are nested within individuals, we use three-level multivariate mixed models including random effects for each level-1 variable (daily observations) allowing for within-day (level 2) and within-person (level 3) variations. In this way, time-varying momentary mindfulness and self-control on level 1 (daily observations) will be predicted by day (level 2) and group (level 3), controlling for age, gender, social desirability and other personality traits at level 3. Significant main effects of the variables day and group would indicate group differences and a change of momentary mindfulness and self-control across time. Furthermore, significant two-way interactions between the continuous variable day (level 2) and the categorical variable group (level 3) would indicate an effect of mindfulness training on momentary mindfulness and self-control relative to the control condition in everyday life.

The secondary outcomes habitual mindfulness and self-control are examined using mixed models. Two-way interactions between laboratory meetings (seven meetings) and group (mindfulness versus control) predicting habitual mindfulness and self-control would indicate differences between groups from one meeting to another. Further additional momentary and habitual measures will be examined in a similar manner.

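### The stated 95% power belongs to a static group difference in mindfulness, not to the day-by-group interaction that the plan uses to judge the training

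*Protocol article*

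**What the plan says.** The Sample size section states its target: a calculation for multilevel models "to detect group differences in state and trait mindfulness between individuals". Its inputs are:

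- ICC: "we assume an unexplained intraclass correlation (ICC) of 0.25"
- power: "want to achieve a power of 1 − *β* = .95"
- significance level: "set an alpha level *α* = .05 for a two-sided test"
- effect: "to detect a medium difference of Cohens’s *d* = .33 between conditions"

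It concludes: "Thus, this leads to a sample size of *N* = 120 to detect medium group differences between individuals". Allowing for about 10% attrition gives 134. The section mentions no time trend, no difference in slopes and no variance of individual slopes.

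The section Primary and secondary outcome analysis fits three-level mixed models with day and group as predictors. Main effects of day and group are read as change over time and as group differences. It is the two-way interaction of continuous day with group that "would indicate an effect of mindfulness training on momentary mindfulness and self-control relative to the control condition in everyday life". The secondary outcomes are handled likewise, through meeting by group.

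On timing, the Intervention section says: "The mindfulness training starts 1 week after the first laboratory meeting". The diary starts one day after that first meeting (Ambulatory Assessment protocol), and the caption of Fig. 2 calls days 1 to 6 baseline.

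**The concern.** The sample size and the analysis address different parameters. The first is a difference in level between conditions. The second is a difference in the rate of change. An effect size and an ICC determine the power of the first. The power of the second also needs the shape of the effect over time and the between-person SD of the slopes.

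At stake is how the result will be read. The article gives one power figure. If the interaction is not significant, a reader will set that result against 95% and may conclude that a medium training effect has been ruled out with high confidence. The calculation does not license that inference.

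**Working it through.** **1. Reproducing the plan's figure.** Take the mean of m prompts per person, with total variance 1 and ICC .25. The variance of a person mean is v = .25 + .75/m. For two equal arms, total N = 4(1.96 + 1.645)² v / .33², and power at 60 per arm is Φ(.33/√(2v/60) − 1.96).

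| m | v | N (unrounded) | power at 60 per arm |
|---|---|---|---|
| 1 | 1.0000 | 477.3 | 43.9% |
| 6 | .3750 | 179.0 | 83.9% |
| 40 | .2688 | 128.3 | 93.7% |
| 204 (days 7–40, six a day) | .2537 | 121.1 | 94.8% |
| 240 (days 1–40, six a day) | .2531 | 120.8 | 94.9% |
| no limit | .2500 | 119.3 | 95.1% |

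N = 120 is therefore sound as a comparison of person means over a large number of prompts, with no time term. The attrition step also holds: 120/.9 = 133.3, rounded up to 134. The arithmetic cannot show which prompts were meant, since 204 and 240 both fit.

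**2. What the powered effect implies for the declared test.** With days 1 to 40, the mean day is 20.5 and Sxx = Σ(day − 20.5)² = 5330. The fitted slope of the group difference is Σ(day − 20.5)·δ(day)/Sxx. If δ(day) = .33 on every day, the numerator is .33 × 0 = 0. Under exactly that effect the interaction test rejects only at its 5% level.

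**3. Power of the interaction under stated assumptions.** The documents give no slope inputs, so the following are assumed:

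- 60 per arm and complete diaries with six prompts a day;
- a group difference growing linearly from 0 on day 1 to .33 on day 40;
- residual variance .75, of which a part w between 0 and .2 lies at day level;
- τ, the SD of individual day-1-to-day-40 trends, in total-SD units.

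The variance of a day mean is w + (.75 − w)/6, which is .125 at w = 0 and .2917 at w = .2. The sampling variance of one person's estimated 39-day change is that value × 39²/5330, giving .0357 and .0832. Power is Φ(.33/√(2(τ² + e)/60) − 1.96), with e the sampling variance.

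Worked case, τ = .5 and w = 0: √(2 × .2857/60) = .0976; .33/.0976 = 3.38; Φ(3.38 − 1.96) = 92%.

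| τ | power, w = 0 | power, w = .2 |
|---|---|---|
| .3 | 99.9% | 99.1% |
| .4 | 98.3% | 95.6% |
| .5 | 92.2% | 87.9% |
| .7 | 70.3% | 66.5% |

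Power equals 95% only where τ is about .46 (w = 0) to .41 (w = .2).

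**4. Trajectory matters too.** A full .33 from day 7 onward gives a fitted 39-day change of .33 × 102/5330 × 39 = .25, where 102 = 6 × (20.5 − 3.5) comes from the six baseline days. A linear rise that starts on day 7 and reaches .33 on day 40 gives .36. The same end-of-study difference therefore yields more or less interaction power according to its path.

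**The case against.** The strongest reply is that the Sample size section misstates nothing. It names its target as group differences in mindfulness and never attaches 95% to the interaction. The group main effect is also a term in the planned model, and the article describes these analyses as exploring the effect. It is fair to call the power statement incomplete rather than false. The reply does not remove the mismatch, because the analysis section assigns the training effect to the interaction, and a main effect taken over all 40 days would include the week before training.

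The power might also be better than stated. With an ICC of .25 the between-person SD is .5. If that variance is centred mid-study, τ = .7 implies a correlation between true day-1 and day-40 levels of (.25 − .1225)/(.25 + .1225) = .34, which is low. The article quotes a test-retest correlation of .82 for the trait mindfulness scale. If momentary levels were as stable, τ would be about .31 and linear-case power about 99% or more. That borrows a trait figure whose retest interval is not given, but it shows that the low end of the table should not be taken as the expected case.

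Three stronger readings are tempting and are not supported:

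- **The trial is underpowered.** The direction is unknown without a slope SD and a trajectory.
- **The calculation assumes a .33 effect on all 240 prompts, including those before training.** The article gives no number of prompts for the calculation, and 204 post-training prompts reproduce N = 120 equally well. Any loss of power from the baseline week is not a demonstrated property of the plan.
- **Momentary self-control has low power.** The article gives no effect size for it, so any figure would be invented, and a condensed article may leave that calculation to the full protocol.

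**Conclusion.** The point stands in limited form. N = 120 at 95% power is correctly calculated for a static difference in mindfulness between conditions, and the two passages show that this is not the contrast declared as the training effect. That conclusion needs no assumption. The size does: under linear divergence to .33 with 60 per arm, interaction power runs from about 99% or more down to 67–70% as the SD of individual 40-day trends goes from .3 to .7. The documents do not say where in or beyond that range the trial lies. It is a correction to the power statement, not evidence that the sample is too small.

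**What to change.** Keep N = 120 analysed and 134 enrolled; the allocation sequence of 134 already exists. In the Sample size section:

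1. State that the 95% applies only to a static group difference in mindfulness of d = .33.
2. Report power at N = 120 for the day-by-group test. If a baseline-adjusted difference at the end of training is made the primary contrast instead, report power for that.
3. Take the slope SD from the laboratory's earlier diary studies, since the ICC already rests on its previous research. Show a range around it, and fix one effect trajectory for the whole table.

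The cost is a few sentences and one short calculation. The stated figure may turn out less favourable than 95%, or more so. Recruitment and data collection are unaffected, and so are the planned models unless the primary contrast is changed.
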